
### Safety

Operation procedures will strictly follow the latest safety guidelines for TMS (Rossi et al., 2009), and participants will be screened strictly in accordance with the inclusion and exclusion criteria to minimize the risk of adverse event. Common adverse events of TMS include (but are not limited to) headache, dizziness, tinnitus, and seizures. If mild headache, discomfort caused by noise, and scalp irritation occur, they are usually self-healing and transient. Hence, before testing or intervention, the patient should be informed of the risks in advance. Seizures, the most severe TMS-related adverse event with a crude risk of approximately 0.02% (Rossi et al., 2009), are expected to occur only during or immediately after stimulation. In addition, any adverse event occurring within 24 h after MRI will be reported. If a serious incident occurs, it will be immediately reported to the principal researcher and ethics committee. The ethics committee will assess whether the patient should receive further treatment. If the patients suffer from syncope, seizures, and other conditions that may affect the subject’s health during the treatment, we will stop the assigned intervention. Once the participants are injured during this trial, they will be compensated. All adverse events from TMS will be reported by the researcher and recorded on the case report form. The researchers will record the date, duration, and severity of adverse events.

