## Introduction

Every year, over 15 million people in the world suffer from stroke (Van Lieshout et al., 2017). Balance problem is a common dysfunction that arises after stroke and is usually due to poor proprioception, decreased motor control, and abnormal integration of nervous system (Xiong et al., 2019). Moreover, the balance problem may be the main cause of poor walking ability and increased risk of falls in patients with stroke (Zhang et al., 2020). About 15–37% of patients with stroke fall down at least once due to balance dysfunction during hospitalization (Rabadi et al., 2012). Falls appear to be frequent after discharge, with approximately 40% falling within 6–12 months of stroke (Wada et al., 2007). Therefore, balance plays a significant role in the rehabilitation process of stroke. However, pharmacotherapy (Mead et al., 2013) and conventional rehabilitation treatments, including core strength exercises (Chung et al., 2014), visual feedback training (Zhang et al., 2020), neurodevelopmental therapy (Langhammer and Stanghelle, 2011), and proprioceptive neuromuscular facilitation (Eng and Tang, 2007) performed unsatisfactory results on balance recovery among stroke patients.

In recent years, repetitive transcranial magnetic stimulation (rTMS), a non-invasive brain stimulation technology, has been widely used in various nervous system diseases (Ren et al., 2019; Yin et al., 2020). rTMS induces a current in the cerebral cortex through a coil that generates a magnetic field, thereby regulating the excitability of the cerebral cortex and affecting neuroplasticity (Brown et al., 2021). Theta burst stimulation (TBS), a novel pattern of rTMS, has the characteristics of lower stimulation intensity and a shorter stimulation session (2–3 min or less) (Pinto et al., 2018), the relatively low stimulation intensity reduces the risk of adverse reactions especially the risk of epileptic seizures (Gutierrez-Muto et al., 2020). Huang and Rothwell (2004) were the first to investigate the neurophysiological effects of TBS in healthy human subjects, founded that 600-pulse intermittent TBS (iTBS) can enhance cortical excitability.

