### Blind

This study is a participants and assessors-blinded study. Given the nature of the iTBS intervention, blinding the physicians performing the intervention is impossible. The intervention team needs to be separated into blinded physicians performing routine rehabilitation treatment, and unblinded physicians exclusively applying iTBS. However, patients, outcome assessors, research assistants, and statisticians will be blinded. For urgent unblinding, researchers can use sealed envelopes labeled with the patients’ randomization numbers. To maintain the quality of the trial, a patient’s allocation must be unblinded only in exceptional circumstances when knowledge of the actual treatment is essential for the management of the patient.

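### The case-report-form rule covers adverse events from TMS, so a non-serious event that nobody attributes to stimulation, such as a fall without serious injury, has no stated recording route

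*Protocol article*

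**What the plan says.** The Safety section of the protocol article sets these rules for capturing events:

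- The main rule: "All adverse events from TMS will be reported by the researcher and recorded on the case report form".
- A rule tied to scanning: "any adverse event occurring within 24 h after MRI will be reported". The Study Design section places the rs-fMRI scans at baseline and at 3 weeks.
- A rule for serious events: "If a serious incident occurs, it will be immediately reported to the principal researcher and ethics committee".
- The details to be taken down: "The researchers will record the date, duration, and severity of adverse events".
- The expected class of events: "Common adverse events of TMS include (but are not limited to) headache, dizziness, tinnitus, and seizures". Falls are not named.

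The Blind section separates staff into blinded physicians giving routine rehabilitation and "unblinded physicians exclusively applying iTBS". It adds that "patients, outcome assessors, research assistants, and statisticians will be blinded". Neither section says who decides that an event comes from TMS.

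The Introduction links poor balance to a raised risk of falling and states: "About 15–37% of patients with stroke fall down at least once due to balance dysfunction during hospitalization". The Inclusion Criteria admit patients with Berg scores of 0 to 40.

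**The concern.** The main rule applies a causal test before an event is written down. An event that fails the test is not recorded as unrelated; under this rule it is not recorded at all. That matters for two reasons.

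First, completeness. In a balance trial that enrols patients with poor balance, a fall is an obvious safety event. It is also one that staff can easily put down to the stroke. The rule then gives them no reason to enter it.

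Second, comparability. If the judgement is made, or coloured, by someone who knows the arm, the same event may be accepted as related in one arm and dismissed in the other. Any later table of events by arm would mix the true event rate with the attribution rate, and events never written down are hard to recover reliably.

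**Working it through.** The plan states no figure on this point, so the main check is to follow events through the wording. The arithmetic after it only illustrates scale.

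**Step 1. Which events have a stated route?**

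| Event | Route in the Safety section | Causal judgement needed first? |
|---|---|---|
| Headache, dizziness, tinnitus, seizure | Listed as common TMS events; case report form | Largely settled by the list |
| Any event within 24 h after a scan | MRI rule | No |
| Serious incident, including a seriously injurious fall | Principal researcher and ethics committee | No |
| Fall without serious injury, outside 24 h after a scan | Only the main rule | Yes |
| Other non-serious, unlisted event outside 24 h after a scan | Only the main rule | Yes |

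The last two rows are the gap. The MRI rule covers any adverse event, while the TMS rule in the same section is limited by cause, so the difference in scope is in the text. The sentence on date, duration and severity carries no limit of its own. It follows directly on the restricted sentence and most naturally says which details to take, and it includes no field for relatedness.

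**Step 2. How much of the course does the MRI rule cover?** With two scans, the windows total 2 × 24 h = 2 days. Fifteen sessions, Monday to Friday over three consecutive weeks, span 5 + 7 + 7 = 19 calendar days when the course starts on a Monday. The scans are at baseline and at 3 weeks, so the windows lie at or beyond the ends of that span.

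**Step 3. Scale, using the document's own fall risk.** Inputs: p = 0.15 to 0.37 (Introduction) and n = 20 per arm (Sample Size). Expected patients with at least one fall = n × p.

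- Per arm: 20 × 0.15 = 3.0; 20 × 0.37 = 7.4.
- Both arms: 40 × 0.15 = 6.0; 40 × 0.37 = 14.8.

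These are not forecasts for this trial. The risk is for a whole hospitalization, and some falls would be caught by the other routes.

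**Step 4. What differential attribution could do.** Recorded fallers = n × p × a, where a is the chance that a fall is attributed to TMS. The document gives no value of a; those below are assumptions, with the true fall risk equal in both arms.

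| p | a, active / sham | Recorded, active / sham |
|---|---|---|
| 0.37 | 0.5 / 0.5 | 7.4 × 0.5 = 3.7 / 3.7 |
| 0.37 | 0.5 / 0.1 | 3.7 / 7.4 × 0.1 = 0.7 |
| 0.15 | 0.5 / 0.5 | 3.0 × 0.5 = 1.5 / 1.5 |
| 0.15 | 0.5 / 0.1 | 1.5 / 3.0 × 0.1 = 0.3 |

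Equal attribution loses half the fallers but keeps the arms comparable. Unequal attribution creates a difference where none exists. With recording regardless of cause, a = 1 in both arms and both problems disappear.

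**The case against.** The strongest reply is that this is a condensed article. Event definitions, form items and relatedness fields usually sit in the full protocol or in operating procedures, which the Research Quality Assurance section mentions. On that view the words limiting the rule to TMS are loose summary writing. This stands as far as the absence of a fall item or a relatedness field goes: neither absence is a fault in itself. It does not remove the point, because the article states a rule and the rule contains a causal filter.

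Several stronger readings are tempting, and the document does not support them.

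- *That every event not blamed on TMS goes uncounted.* Serious incidents are reported whatever the cause, events within 24 h after MRI are covered, and the promise to compensate injured participants presupposes that injuries are noticed.
- *That dizziness later in the day would be missed.* Dizziness is already listed as a common TMS event.
- *That unblinded physicians make the causal judgement.* The text says only that the researcher reports. That person could be blinded, and blinded physicians see the patient immediately after each session for 60 min of rehabilitation. The fault is that nothing assigns the judgement to a blinded person.
- *That a planned safety comparison is biased.* Safety is not a listed outcome and the article describes no such analysis. The bias would arise only if counts by arm were later reported.
- *That 3 to 7 fallers per arm would be lost.* The cited risk covers a different period, and part of it would be caught elsewhere.
- *That harm to balance would go unseen.* The Berg Balance Scale is scored weekly by blinded assessors and could show a worsening by itself.

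**Conclusion.** The point holds in a limited form. Followed as written, the Safety section gives no stated recording route for a non-serious adverse event that is not attributed to TMS and falls outside 24 h after a scan. A fall without serious injury is the case that matters most in this population. The attribution step is not assigned to anyone blinded, while the physicians delivering iTBS know the arm.

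The number of events affected is unknown. It depends on the 3-week fall risk, which is probably below the cited 15–37%, on the share of falls that are non-serious, and on how often staff attribute them to stimulation. The document gives none of these. That attribution would differ between arms is a possibility, not something shown. The primary efficacy analysis is not affected. What is at risk is the completeness and fairness of any account of harms by arm. The correction is cheap and is best made before or early in enrolment, so it is worth making.

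**What to change.** Replace the sentence that limits the case report form to events from TMS with a rule of this kind: *every adverse event in either arm, from the first session to the last assessment, is entered on the case report form regardless of suspected cause.* Then:

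- Ask each patient about falls since the last visit at the existing weekly assessments, by the blinded assessor. Asking after the Berg scale has been scored keeps the answer from colouring the score.
- Record relatedness afterwards as a separate field, judged by someone blinded to arm.
- Report, by arm, the number of patients with at least one event and the number of events, with falls shown separately.

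The MRI and serious-incident rules can stay as they are. The cost is one extra line on the form at visits that already take place, a relatedness field, and slightly more event recording. Treatment and visit schedules do not change.

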### Patient and Public Involvement

During the trial, patients will not participate in the design, implementation, or outcome assessment of the study. However, we plan to publicize our research proposal to participants and the public through the official website of the hospital (such as WeChat official account) and lectures at major academic conferences.

### Ethics and Dissemination

The study has been approved by the Medical Research Ethics Committee of Wuxi Mental Health Center (Wuxi Tongren Rehabilitation Hospital). Before entering the study, all participants will be informed that their participation are entirely voluntary and that they can withdraw from the trial at any time without consequence. During the trial, the welfare and rights of participants should be satisfied, and the privacy of patients should be guaranteed. Any change in the key aspects of the protocol, such as inclusion criteria, observation indicators, and statistical analysis, will be submitted to the Medical Research Ethics Committee. Results will be presented at conferences and submitted to peer-reviewed journals.

### Research Quality Assurance and Management

Researchers should perform their respective responsibilities. Including the following contents:

1.The principal researcher establishes unified experimental test indices, standard operating procedures, and quality control procedures.2.Researchers participating in our trials must have professional expertise and the ability to conduct clinical trials. Moreover, invariability of personnel involving in this research should be guaranteed.3.The interveners and evaluators need to participate in standardized training before the trial, they should adopt standard operating procedures to ensure the quality of clinical trials.4.The principal researcher shall appoint an inspector to ensure that the rights and interests of participants are protected, that the trial follows approved protocols, and that reports are accurate.

## Discussion

This 3-week randomized controlled clinical trial aims to study whether cerebellar vermis iTBS can improve balance function in patients with stroke. In this perspective of experiment design, our study puts forward some methodological concerns that should be discussed, including the large variation in balance function among enrolled patients. Therefore, a stratification approach will be adopted in this study to divide all participants into two subgroups in accordance with the BBS. In addition, we set a sham stimulation group to eliminate the placebo effect of iTBS intervention. After careful consideration of all factors, including the feasibility of the study and the treatment time pattern of the hospital where the experiment will be conducted, we set sessions from Monday to Friday for 3 weeks. Also, outcome will be evaluated at pre-intervention, the end of first, second, and third week of post-intervention. We want to compare the efficacy at different time points, and to explore the earliest time when the treatment can take effect. Our study will use rs-fMRI rather than task state fMRI for measuring the iTBS-induced effects, although task state fMRI can reflect the fMRI images of the brain when performing specific tasks. What we considering is that our subjects are post-stroke patients with motor dysfunction, there may be great differences in the quality of tasks completed by stroke patients, which may affect the results.

In this study, we expect that the cerebellar vermis iTBS can promote the recovery of balance function after stroke. This hypothesis is based on the following evidence.

Maintaining balance depends upon a complex coordination and integration of multiple systems in the body, including the visual system, vestibular system, and auditory system. As pointed out in fMRI research, the cerebellar vermis and the visual network have a strong functional connection (Kellermann et al., 2012; Li et al., 2012). Recent evidence displayed that the vermis coordinates eye and body movements, and provides visual and auditory input related to balance (Fujita et al., 2020). In addition, studies have shown that the vermis participates in regulating vestibular system and maintaining head position (Lam et al., 2016). Balance is best maintained when all inputs are integrated together. Therefore, the cerebellar vermis plays an essential role in the active maintenance of body balance.

In addition, the process of maintaining balance involves a close cooperation between the cerebellum and the cerebrum. These interconnections are facilitated by white-matter tracts with the following connective pathways: the cortico-ponto-cerebellar pathway and cerebello-thalamo-cortical (CTC) pathway (Iwata and Ugawa, 2005; Opie and Semmler, 2020), which have been proven to be involved in motor coordination (Spampinato et al., 2020). As pointed out in an animal experiment, the reduction of ipsilateral cerebral cortical activity can lead to the reduction of contralateral cerebellar activity and metabolism (Baek et al., 2020). Previous studies similarly confirmed that the cerebellum establishes strong anatomical and functional connections with the M1 area through the cerebellum–thalamic–M1 circuit (Maurer et al., 2016). The cerebellum has three functional areas, the spinocerebellum, the cerebrocerebellum and the vestibulocerebellum. The vermis classically belongs to the “spinocerebellum” and to receive somatic sensory input from ascending spinal pathways. Cattaneo et al. (2014) pointed out that compared to cerebellar hemispheres, cerebellar vermis takes a more prominent role in continuous visual processing in visual feedback loops. Interestingly, in Coffman et al.’s (2011) study, the rabies virus was injected into the lobule of the vermis, and retrograde transneuronal transport of the virus was used to define disynaptic inputs to it. It was found that large numbers of neurons in the primary motor cortex and other motor areas on the medial wall of the hemisphere project to the vermis. This implicates that there is potential connection between cerebellum vermis and motor area of cerebral cortex. Therefore, iTBS may improve balance by regulating the excitability of the cerebellar vermis, then promoting excitability changes in motor areas of the cerebral cortex.

In current studies, the depth of coil stimulation is an important factor affecting the efficacy of rTMS. Recent studies showed that an eight-figure coil has mostly been used for iTBS (Li et al., 2018). This coil is characterized by small stimulation area, shallow stimulation depth, and good focusing. The range of the magnetic field induced by rTMS attenuates with increasing distance from the scalp surface (Deng et al., 2013). However, the cerebellum is located in the posterior fossa and covered by the tentorium cerebellum, which is deeper from the skull. Previous studies found that the double-cone coil can achieve deeper stimulation effects (Deng et al., 2013) and generate stronger electric field than the eight-figure coil (Mai and Ueno, 2017), confirming good reliability and validity. In addition, Hardwick et al. (2014) showed that the double-cone coil causes the most evident cerebellar brain effect in magnetic stimulation with the same parameters compared with the eight-figure and airfoil coils, suggesting that the double-cone coil may be suitable for studies of TMS over the cerebellum.

In our trial, the location of cerebellar vermis is consistent with similar literatures (Cattaneo et al., 2014; Tan et al., 2021), In Cattaneo’s study, the accuracy of this localization method was further verified by using a neuronavigation system in some subjects for whom structural MRIs were available. The results shown that the scalp coordinate 1 cm below the inion indeed corresponded to the cerebellar vermis (Cattaneo et al., 2014). This research is the first study to explore the effect of cerebellar vermis iTBS on balance dysfunction after stroke by using the double-cone coil. This protocol proposes a rigorous randomized parallel controlled trial design that meets the methodological requirements of full concealment, randomization, and placebo control.

Intermittent theta burst stimulation has the advantages of short stimulation time, easy promotion, and relatively easy application. We hope that the results of this study can shed light on this potential effect. We believe that the current protocol and our results will have important implications for the treatment of post-stroke patients with balance dysfunction.

## Ethics Statement

The studies involving human participants were reviewed and approved by the Medical Research Ethics Committee of Wuxi Mental Health Center (Wuxi Tongren Rehabilitation Hospital) (No. WXMHCIRB2021LLky132): Effect of cerebellar vermis iTBS on the balance dysfunction of stroke patients and the brain remodeling mechanism. The patients/participants provided their written informed consent to participate in this study.
